## Abstract

**Background:**

Dementia is often associated with Neuropsychiatric Symptoms (NPS) such as agitation, depression, hallucinations, anxiety, that can cause distress for the resident with dementia in long-term care settings and can impose emotional burden on the environment. NPS are often treated with psychotropic drugs, which, however, frequently cause side effects. Alternatively, non-pharmacological interventions can improve well-being and maintain an optimal quality of life (QoL) of those living with dementia. Other QoL related outcomes, such as pain, discomfort and sleep disruption are relevant outcomes in music trials as well. Music therapy is a non-pharmacological intervention that can reduce NPS and improve well-being, and its associated symptoms in dementia.

**Methods:**

The research will be conducted at eight nursing home facilities of a health care organization in the Netherlands. A sample size of 30 in each group (experimental and control group) is required, totalling 60 residents increased to 80 when considering expected drop out to follow up. The participants in the intervention group receive 30 min of individual music therapy (MT) in their own room by a music therapist twice a week for 12 weeks. The participants in the control group will receive 30 min of individual attention in their own room by a volunteer twice a week for 12 weeks. Assessments will be done at baseline, 6 weeks and 12 weeks. An independent observer, blinded for the intervention or control condition, will assess directly observed well-being (primary outcome) and pain (secondary outcome) before and after the sessions. Nurses will assess other secondary outcomes unblinded, i.e., perceived quality of life and NPS, both assessed with validated scales. The sleep duration will be indirectly assessed by a wrist device called MotionWatch. Information about psychotropic drug use will be derived from electronic medical chart review.

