There is a growing consensus that quality of life is an important outcome for assessing the effectiveness of interventions for dementia in clinical trials even though it concerns a multidimensional construct influenced by a variety of factors [7, 8]. An observational study in 288 nursing home residents with dementia, showed that NPS such as agitation and depression were particularly strong predictors of poor QoL [9]. These results underline the growing awareness that NPS independently decreases QoL in moderate and severe stages of dementia [9]. Pain is highly prevalent in nursing home residents [10, 11] and can also cause NPS and influences their quality of life directly [12]. Nursing home residents with severe cognitive impairment who have difficulty expressing pain may manifest it through agitation, aggression, or withdrawal [10]. Pain in dementia may express itself also through vocalizations (e.g., crying, screaming, noisy breathing), specific facial expressions (e.g. grimacing) and body language such as restless behaviour [13, 14].

Another factor that may reduce QoL of people with dementia is a deterioration of sleep quality. Sleep disturbances include poor sleep efficiency and increased night awakenings. Petrovsky [15] used domains of Lawton’s framework for quality of life in persons with dementia to synthesize current knowledge on the association between sleep disruption and quality of life in persons with dementia. Sleep disruption was negatively associated with all of four QoL domains (physical functioning, social/behavioral functioning, emotional well-being and cognitive function). In sum, neuropsychiatric symptoms, in relation to or provoked by pain and sleep disturbances, reduces QoL in people with dementia.

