### Secondary outcomes measures

Secondary outcomes are also assessed in all /participating residents and include pain, quality of life, neuropsychiatric symptoms (agitation, anxiety, symptoms of depression), quality of sleep and psychotropic drug use.

**Pain** will be assessed by a blinded research assistant at baseline, six weeks and twelve weeks during 2 min before and after the intervention session or individual attention with the PAIC-15 (Pain Assessment in Impaired Cognition) [54, 55] which is an observational assessment instrument that lists 15 items and uses scores from 0 to 3 for each item. PAIC-15 comprises three domains: facial expression, body movements and verbalizations/vocalizations. Each domain has 5 items and the total score is the sum of all items, ranging from 0 to 45. The research assistant will be trained in using the PAIC-15.

**Quality of life** will be rated by non-blinded nurses at baseline (T0), at six weeks (T1) and at twelve weeks (T2) with the Quality of Life in Late-Stage Dementia Scale (QUALID) [56] that can be used with late-stage dementia patients in institutional settings and has been designed for proxy-rating by nurses. Responses reflect patient behavior over the past seven days. The QUALID consists of eleven items that are short and simple and is characterized by a good reliability and validity and the Dutch translation was a valid measure for quality of life in patients with advanced dementia [57]. The total score is the sum of all items, ranging from 11 to 55. Lower scores indicate a higher quality of life.

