**Physical activity**: rest-activity data will be collected by a MotionWatch (CamNtech Ltd, Cambridge, UK). The MotionWatch measures the arm movements of the participant; based on these movements, the rest-activity and physical activity are determined. It quantifies accelerations due to motor activity of the arm and integrates these over I-minute periods. The MotionWatch has the size and shape of a watch, is worn on the dominant wrist. The participants will be asked to wear the MotionWatch twenty-four hours a day for 1 week in the week before the intervention starts (T0) and the week directly after the last intervention session (T2). Nurses are asked to temporarily take off the MotionWatch when the participant takes a shower, performs another activity in which the MotionWatch could be exposed to too much water. Nurses will report the time that devices are taken off. Five parameters are calculated: Interdaily Stability (IS), Intradaily Variability (IV), Relative Amplitude (RA), most active period of 10 h and least active period of five hours. First, the IS variable that quantifies the strength of coupling between the rest-activity rhythm and supposedly stable Zeitgebers (e.g., meals) is calculated. IV, which quantifies the fragmentation of the rhythm, that is, the frequency and extent of transitions between rest and activity. RA quantifies the difference between the main activity (day) and rest (night) periods. The parameter of 10 most active hours (M10) is used to determine the amount of physical activity. The parameter (L5) are least active periods of five hours to determine rest activity.

Data on chronic psychotropic drug use will be derived from the electronic medical chart. Psychotropic drugs will be categorized into antipsychotics, anxiolytics, hypnotics, antidepressants and anti-dementia drugs according to the Anatomical Therapeutic Classification (ATC) system.

Any attrition or adverse effects of the interventions will be documented. The interventions will be discontinued if, in consultation with the physician or psychologists, harmful effects are observed and are expected to continue with exposure to any of the two interventions.

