#### Data analysis

Immediate effects are defined as the difference in change between outcomes 15 min before and after the intervention sessions. Cumulative effects are effects over time not including those immediately after the session (i.e., built-up effect over time and measured before the session in order not to include possible immediate effects of the session). Overall effects are effects over time including those immediately after the session. Immediate, cumulative and overall effects are analyzed with mixed model analysis to consider the dependency of the repeated observations within the patient.

For the immediate effects, the outcome will be the post-test (T1b, T2b) and adjustment will be made for the pre-test (T1a, T2a). For the cumulative effect, the outcome will be the pre-test and an adjustment will be made for the baseline. For overall effects, the outcome will be post-test and adjustment will be made for the baseline.

For all treatment effects, effects at the different time-points will be analyzed by adding a time x treatment interaction to the mixed model analysis. Furthermore, both crude and adjusted (adjustments for gender, age, cognitive deterioration and for medication use, which will be added as a time-dependent covariate) will be performed. In the mixed-model analysis, we will also evaluate whether an adjustment for the correlated observations within facilities is necessary. There is no need to impute missing data because mixed models can handle missing assessments.

In explorative post-hoc analysis we will evaluate whether the intervention effects will be different for patients with a musical background by adding the interaction between the intervention variable and presence of musical background.

Sleep quality data of the MotionWatch (CamNtech Ltd, Cambridge, UK) will be analyzed with Motionware software version 1.2.1. Five parameters will be calculated: Interdaily stability, Intradaily variability, Relative Amplitude, most active period of 10 h and least active period of five hours. The 5 parameters will be analyzed with linear regression analyses with the values measured after the intervention period as outcome with an adjustment for the baseline vale of particular outcome.

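### Sleep duration and quality of sleep are named as outcomes, but the five planned actigraphy parameters describe rest-activity rhythm: none measures duration, and three are at most indirect proxies for quality

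*Protocol article*

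**What the plan says.** The sleep outcome appears under several names in the protocol article.

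- **Abstract, Methods:** a duration. "The sleep duration will be indirectly assessed by a wrist device called MotionWatch".
- **Secondary outcomes measures, opening sentence:** the list ends with "quality of sleep and psychotropic drug use". Rest-activity rhythm and physical activity are not in that list.
- **Background and rationale:** sleep disturbance, with NPS and pain, is one of three symptoms that motivate the trial. Examples are given: "Sleep disturbances include poor sleep efficiency and increased night awakenings".
- **Secondary outcomes measures, device paragraph:** this stands under the label Physical activity. The watch records arm movement and, "based on these movements, the rest-activity and physical activity are determined".
- **Table 1:** the row is called rest/activity (actigraphy), with recordings at T0 and T2b only.
- **Data analysis:** the same data are introduced as sleep quality data, followed by "Five parameters will be calculated: Interdaily stability, Intradaily variability, Relative Amplitude, most active period of 10 h and least active period of five hours". Each parameter is analysed by linear regression of the follow-up value, adjusted for baseline.

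The device paragraph gives the same five parameters and explains each one.

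**The concern.** The outcome that is named and the quantities that are calculated do not match. A reader of the abstract expects a between-group difference in sleep duration, and a reader of the outcome list expects one in quality of sleep. The analysis delivers differences in five rest-activity parameters, and the article describes no step that turns them into either.

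What is at stake is interpretation. Because Data analysis labels the five parameters as sleep quality data, a difference in M10, which the protocol itself assigns to physical activity, could be reported as better sleep. A null result on all five could be reported as no effect on sleep although sleep duration was never estimated.

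**Working it through.** The plan states no figure on this point, so there is none to reproduce. The check has three steps.

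**1. Each parameter against the named outcomes, using the protocol's own descriptions**

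| Parameter | What the device paragraph says it reflects | Sleep duration? | Sleep quality? |
|---|---|---|---|
| IS | coupling of the rhythm to regular time cues | no | no |
| IV | "IV, which quantifies the fragmentation of the rhythm, that is, the frequency and extent of transitions between rest and activity" | no | partial proxy (fragmentation) |
| RA | contrast between daytime activity and night rest | no | partial proxy (night rest) |
| M10 | amount of physical activity | no | no |
| L5 | rest activity over a window of fixed length | no, the length is set at five hours | partial proxy (night rest) |

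Duration: 0 of 5. Sleep efficiency or night awakenings measured as such: 0 of 5. Partial proxies for quality: 3 of 5.

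**2. Why M10, L5 and RA cannot carry duration**

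Assume the usual form RA = (M10 − L5)/(M10 + L5), an activity level of 100 awake and 5 asleep, and one unbroken sleep block of 6 to 10 h.

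- Every such block is longer than 5 h, so L5 lies wholly inside sleep: L5 = 5.
- Wake time is 24 − 10 = 14 h to 24 − 6 = 18 h, always more than 10 h, so M10 lies wholly inside wake: M10 = 100.
- RA = (100 − 5)/(100 + 5) = 95/105 = 0.905.

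None of the three depends on how long the person slept within that range.

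**3. All five parameters on simulated data**

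Assumptions: 7 days of minute-level activity, the levels above, gamma noise, sleep centred at 03:00, and hourly means for IS and IV.

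| Sleep (h) | IS | IV | RA | M10 | L5 |
|---|---|---|---|---|---|
| 6 | 0.967 | 0.509 | 0.905 | 99.6 | 4.98 |
| 7 | 0.972 | 0.278 | 0.908 | 101.1 | 4.87 |
| 8 | 0.979 | 0.396 | 0.908 | 100.6 | 4.83 |
| 9 | 0.975 | 0.258 | 0.905 | 100.5 | 5.00 |
| 10 | 0.980 | 0.381 | 0.906 | 100.7 | 4.97 |

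Four hours more sleep leaves IS, RA, M10 and L5 almost unchanged. IV moves, but down and up, largely according to whether the sleep block starts on a whole or a half hour. Duration cannot be read back from these values.

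The simulation varies only the length of an unbroken block. It contains no awakenings, so it supports the statement on duration and says nothing about quality.

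**The case against.** The strongest reply is that the abstract says the assessment is indirect, that Data analysis in effect adopts the five parameters as the working definition of sleep quality, and that IV, RA and L5 do bear on fragmented sleep and night rest. For quality, much of this stands: the mismatch is partial, and it would be too strong to infer that the five parameters tell us nothing about sleep. For duration it does not stand, because the article gives no route, direct or indirect, from these parameters to a duration. Nor is this detail left to a fuller plan. The article gives a list of exactly five parameters twice, and its own labels disagree.

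Several stronger readings are tempting but unsupported.

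- **That the background defines sleep disturbance as poor efficiency and awakenings.** It says that disturbances include these. That is a remark about the literature, not an endpoint definition.
- **That the trial fails on a main objective.** The Objective section does not name sleep.
- **That the follow-up recording is mistimed.** The week after the last session is stated openly, agrees with the wording in Data analysis, and mirrors the session-free baseline week. Other T2 measures are not all taken at a session either: the nurse-rated scales look back one to four weeks, and medication comes from charts. Moving the recording would change the question rather than correct an error.
- **That five tests carry a 23% false-positive risk (1 − 0.95^5 = 0.226).** This assumes independence, yet RA is built from much the same information as M10 and L5. These are secondary outcomes, and error control for them is commonly left to the analysis plan.

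**Conclusion.** The point holds as a mismatch between the named outcome and the planned quantities. It is complete for sleep duration (0 of 5) and partial for quality of sleep (3 of 5 are indirect proxies, none a direct measure). The article also contradicts itself on the label: sleep duration, quality of sleep, physical activity, rest/activity and sleep quality data all refer to one set of recordings.

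The conclusion rests on taking the two identical lists of five as complete, as they are worded, and on the usual definitions of the parameters. The numerical illustration uses assumed activity levels and is not needed for the conclusion, which follows from the text.

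The consequence is limited to one secondary outcome. The correction is worth making before results are reported, because the current labels allow a rhythm finding to be presented as a sleep finding.

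**What to change.** 1. From the same MotionWatch recordings, derive night-time sleep duration and, where the recording allows, sleep efficiency and night awakenings. Define these as the sleep outcomes.
2. Report IS, IV, RA, M10 and L5 as rest-activity rhythm outcomes, and remove the sleep quality label from them in Data analysis.
3. If sleep variables cannot be derived, rename the outcome rest-activity rhythm in the Abstract, the secondary outcome list and Data analysis, and draw no conclusion on sleep duration.
4. In the report, state that the T2 actigraphy covers the week after the last session.

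**Cost:** some extra analysis of recordings that are already planned, with no new device or visit. One condition needs checking. The article says that nurses note when the watch is taken off, but not that bed and rise times are recorded. If the derivation needs them, a short nightly log in the two recording weeks would be added. Step 3 alone costs only wording.

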**Discussion:**

The main purpose of this study is to assess the effects of individual music therapy on directly observed well-being controlled for individual attention in nursing home residents with dementia with NPS. The outcomes refer to both short-term and long-term effects consistent with therapeutic goals of care for a longer term. We hope to overcome limitations of previous study designs such as not blinded designs and music facilitators that were not only music therapists but also occupational therapists and nurses. This study should lead to more focused recommendations for practice and further research into non-pharmacological interventions in dementia such as music therapy.

**Trial registration:**

The trial is registered at the International Clinical Trials Registry Platform (ICTRP) search portal in the Netherlands Trial Registration number NL7708, registration date 04-05-2019.

## Introduction

### Background and rationale

Dementia is a common disease and in 2021, the World Health Organization estimated that around 55 million people have dementia worldwide [1]. Dementia is a neurodegenerative syndrome characterized by a progressive deterioration of cognitive function, in particular memory but other cognitive domains such as language, praxis, visual perception and most notably executive functions are also often affected [2]. Personality and behavior changes, together with a decline in the ability to perform activities of daily living, may result in a loss of independence. The personality and behavioral changes are often reflected in Neuropsychiatric Symptoms (NPS). More specifically, NPS may express itself in, for example, agitation, disinhibition, irritability, delusions, hallucinations, depression, anxiety and apathy. These symptoms are ubiquitous in nursing home patients with dementia, with overall rates of more than 80% [3].

As there are no curative treatments for dementia yet, it is important to focus on interventions that may have beneficial effects on well-being and maintain an optimal quality of life. Quality of life is defined by the WHO as “individuals’ perceptions of their position in life in the context of the culture and value systems in which they live and in relation to their goals, expectations, standards and concerns” [4]. Well-being is defined in terms of a state of equilibrium existing between personal resources and life challenges that, when achieved, gives rise to positive emotions and psychological health [5]. The constructs of QoL and well-being have often been used inter-changeably in dementia research [6].

There is a growing consensus that quality of life is an important outcome for assessing the effectiveness of interventions for dementia in clinical trials even though it concerns a multidimensional construct influenced by a variety of factors [7, 8]. An observational study in 288 nursing home residents with dementia, showed that NPS such as agitation and depression were particularly strong predictors of poor QoL [9]. These results underline the growing awareness that NPS independently decreases QoL in moderate and severe stages of dementia [9]. Pain is highly prevalent in nursing home residents [10, 11] and can also cause NPS and influences their quality of life directly [12]. Nursing home residents with severe cognitive impairment who have difficulty expressing pain may manifest it through agitation, aggression, or withdrawal [10]. Pain in dementia may express itself also through vocalizations (e.g., crying, screaming, noisy breathing), specific facial expressions (e.g. grimacing) and body language such as restless behaviour [13, 14].

Another factor that may reduce QoL of people with dementia is a deterioration of sleep quality. Sleep disturbances include poor sleep efficiency and increased night awakenings. Petrovsky [15] used domains of Lawton’s framework for quality of life in persons with dementia to synthesize current knowledge on the association between sleep disruption and quality of life in persons with dementia. Sleep disruption was negatively associated with all of four QoL domains (physical functioning, social/behavioral functioning, emotional well-being and cognitive function). In sum, neuropsychiatric symptoms, in relation to or provoked by pain and sleep disturbances, reduces QoL in people with dementia.

Consequently, the question arises if adequate strategies are available for treating this triad of symptoms, i.e. NPS, pain, and sleep disturbances, and hence, improving QoL, in people with dementia. NPS are often treated pharmacologically with psychotropic drugs, which frequently cause unwanted side effects, such as somnolence and extrapyramidal symptoms [16]. Psychosocial interventions, however, may obviate the indication for antipsychotic drug prescriptions [17]. Moreover, therapies such as validation, reminiscence, psychomotor therapy, multisensory stimulation and music therapy can increase QoL of people with dementia and their caregivers [18]. Sikkes et al. reviewed the evidence and found that various non-pharmacologic treatments such as music therapy effectively improve behavior [19].

Music therapy is a non-pharmacological intervention which is used as a treatment for NPS in patients with dementia [20–22]. In the USA, music therapy is defined by the American Music Therapy Association (AMTA) as “the clinical and evidence-based use of music interventions within a therapeutic relationship to accomplish individualized goals by a credentialed professional who has completed an approved music therapy program” [23]. This definition of music therapy and the accompanying AMTA Standards of Practice recommend an individualized treatment process, including referral, building a therapeutic relationship, assessment, observation, targeting individualized goals and objectives, treatment planning, protocol selection and implementation, termination and evaluation [24]. The number of studies examining the effects of music therapy for people with dementia has increased over time [25]. A Cochrane review in 2011 [26] included 10 studies mostly of poor quality and could not draw firm conclusions about the effects of music therapy in the treatment of behavioral, social, cognitive and emotional problems of older people with dementia. In an update of the Cochrane review [27] twenty-two studies were included. The results from the review suggest that music therapy may also improve emotional well-being including quality of life. However, outcomes could be based on recall or direct observation, and not all outcomes are assessed blinded. The results of the review further suggest that providing institutionalized people with dementia with at least five sessions of a music-based therapeutic intervention might reduce NPS. Moreover, individual therapy, compared with group therapy, had larger effects on behavioral outcomes (agitation, aggression and overall behavioral problems).

Indeed, music therapy can be offered via individual treatment, as well as through a group approach [28]. The group approach benefits engagement and social interaction but in advanced stages of dementia, individual music therapy can better reach the residents with communicative limitations. Personalized interventions with music or music therapy may be a predictor of success [20].

In 2010, we conducted a randomized pilot study on individual music therapy in a nursing home in the Netherlands. The intervention group received individual music therapy from a qualified music therapist who used a person-centered approach. The results pointed to possible reduction of NPS in patients who received individual music therapy compared to patients in the control condition who received usual care [29]. The sample size of the pilot study was very small and the outcome assessments were not blinded. Sakamoto [30] conducted an RCT in 2013 with blinded outcome assessment and individual intervention sessions carried out by music facilitators. The study indicated that interactive individualized interventions reduce stress and increase relaxation in individuals with severe dementia immediately after the intervention.

